### Recruitment

Participants will be recruited from primary care and volunteer organisations/drug rehabilitation centres in Pakistan. A detailed Participant Information Sheet (PIS) about the study will be provided to all interested participants. Objectives as well as risks and benefits of participation will be detailed by a trained RA in local language. Participants eligible for study participation will be given at least 48 h to discuss with their family and to decide whether or not to take part. Those willing to participate will complete consent process and baseline assessments within 1 week of consent.

### Intervention allocation

#### Sequence generation

Participants will be randomly allocated to one of the four intervention arms by an independent offsite statistician using a computer-generated random sequence based on a block randomised design [46] until all study data are collected and verified. Once randomised, participants will be allocated a unique study identification number and informed about their intervention allocated groups within 1 week of randomisation.

#### Concealment mechanism

The independent statistician will share the randomised list of participants with the trial manager and he/she will further communicate the allocation information to therapists. It would not be possible to blind the staff delivering intervention and participants to treatment allocation but outcome assessments at each follow-up will be conducted by research staff blind to intervention groups. The therapist will advise participants not to discuss their intervention allocation with researchers doing outcome assessments.

#### Blinding

Those administering assessments at baseline and follow-ups, data entry, and data analysis will be blind to intervention groups. During the trial, periodic data quality checks will be carried out by the trial statistician. The trial statistician will be blinded to intervention allocations. Upon completion of data entry, preliminary data analysis will be carried out prior to un-blinding.

### Data collection method

All participants (intervention and TAU groups) will undergo assessments at baseline, 3rd month (end of intervention) and at 6th month after randomisation. Participants will complete a self- report demographic information sheet (only at baseline) that will collect information related to age, duration of substance misuse, type of substance used etc., the MAP [47], SWEMWBS [42], EuroQoL (EQ-5D) [43] and CSRI [44]. All the assessments will be carried out by trained research assistants at baseline, 3rd month (end of intervention) and at 6th month.

### Plans to promote participant retention and complete follow-up

Recruitment and retention are both an integral part of any drug and alcohol misuse trial due to the highly chaotic nature of this disorder. To increase retention of participants, protocols developed by Scott [48] will be used, where locater information will be recorded for each participant. Scott [48] achieved 95% retention of participants in his study on alcohol abuse. The study team will have regular contact with participants throughout the study period. Participants in the TAU group will be contacted by RA on weekly basis for first 3 months of the study to keep them engaged and retain in the study as well as to keep them well informed of the study’s progress. Both groups will be contacted monthly from 3 to 6 months to promote retention to the study. These contacts maybe done via a brief 5-min phone call.

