**Methods:**

The proposed project will be conducted in three phases. The first phase of the study will focus on cultural adaptation of the interventions through qualitative interviews with key stakeholders. The second phase will be to refine and produce manually assisted interventions. Third and last stage would be to assess the feasibility of the culturally adapted interventions through a factorial RCT. The study will be carried out in Karachi, Hyderabad, Peshawar, Lahore and Rawalpindi, Pakistan. Recruitment of participants will take place from primary care and volunteer organisations/drug rehabilitation centres. A total of 260 individuals diagnosed with SUD (*n* = 65) in each of the four arms will be recruited. The intervention will be delivered weekly over a period of 12 weeks in both individual and group settings. Assessments will be carried out at baseline, at 12th week (after completion of intervention) and 24th week post-randomisation. The analysis will determine the feasibility of recruitment, randomisation, retention and intervention delivery. Acceptability of intervention will be determined in terms of adherence to intervention, i.e. the mean number of sessions attended, number of home assignments completed, attrition rates, as well as through process evaluation to understand the implementation process, context, participants’ satisfaction, and impact of the study intervention. The health resource use and impact on the quality of life will be established through health economic data.

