### Outcomes

#### Primary outcomes: feasibility indicators

Feasibility will be determined by following indicators:Recruitment rates, attendance (number of sessions attended), retention rate and randomisation.Acceptability of interventions based on client satisfaction, adherence rate (the number of sessions attended, number of home assignments completed) and attrition rates.Completeness of assessment by participants.

Meeting the progression criteria of > 50% of recruitment, > 70% of retention, > 60% of attendance, > 70% of adherence, < 30% of attrition and > 70% of assessment completion at study end will determine that a full definitive trial is needed.

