### Risk management: adverse event reporting and harms

Where a Serious Adverse Events (SAE), or Adverse Events (AE) occur for a particular participant, the research team will halt the study for that individual and review: (a) whether to withdraw the participant from the study, and (b) whether to halt the entire project. AEs will be recorded throughout the trial and any AE occurred will be immediately reported to PI within 24 h. This decision will be based on a consideration of the likelihood that the study itself (including the therapy and assessment procedures) contributed to the SAE (thus making it an Adverse Reaction; AR). Information will be gathered including the participant’s and researcher or therapist’s perspective, and the timing of the AE or SAE (e.g. did it occur immediately after a intervention session?) to help inform this review. Where an AR is identified, it will be considered whether this could apply to other participants and therefore if the study as a whole should be halted. This review process will be documented. Adverse Events (AE) are defined here as any untoward, time-limited, worsening in participants’ mental state or leading to a persistent increase in disability or incapacity. The occurrence of AEs will be monitored by the DMEC.

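### In months 0–3 the specified contact differs by arm and no common adverse event enquiry is set, so adverse event detection may differ by arm

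*Protocol article*

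**What the plan says.** The contact schedule is in the Protocol article under Plans to promote participant retention and complete follow-up. For the control arm: "Participants in the TAU group will be contacted by RA on weekly basis for first 3 months of the study". The stated purposes are engagement, retention and keeping participants informed, and a contact may be a short phone call. A schedule shared with the active arms starts only later: "Both groups will be contacted monthly from 3 to 6 months to promote retention to the study". The same section also makes a general promise, "The study team will have regular contact with participants throughout the study period", with no frequency, staff role or content.

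For the active arms the abstract's Methods paragraph gives the contact in the first three months: "The intervention will be delivered weekly over a period of 12 weeks in both individual and group settings". The article has therapists delivering these sessions.

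Under Risk management: adverse event reporting and harms: "AEs will be recorded throughout the trial and any AE occurred will be immediately reported to PI within 24 h". That section draws on the views of the participant and of a researcher or therapist when an event is reviewed, and gives as an example of useful timing information "did it occur immediately after a intervention session". It has the DMEC monitor the occurrence of adverse events. It names no standard question, interval or staff role for finding them.

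The time points common to all arms are under Data collection method: "All participants (intervention and TAU groups) will undergo assessments at baseline, 3rd month (end of intervention) and at 6th month after randomisation". The instruments listed there are a demographic sheet, the MAP, SWEMWBS, EQ-5D and CSRI. None is described as an adverse event enquiry.

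**The concern.** The article defines adverse events as a time-limited deterioration in mental state or a lasting loss of function. Such events mostly come to light when someone speaks to the participant. If the people who speak to participants, and how often they do so, depend on the arm, the number of recorded events can differ between arms even when the true risk is the same.

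Two things are at stake. The DMEC monitors these events and advises on safety, and counts gathered through different contacts are hard to read by arm. In addition, people who drop out of therapy are foreseeable in this population, and they are the ones for whom the article fixes no specific contact before the month-3 assessment. Because an adverse event triggers a pause and a review of whether the participant should be withdrawn, unequal detection could also feed into attrition, which is a progression criterion.

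**Working it through.** The article gives no adverse event rate or detection figure, so there is nothing of its own to reproduce. The check sets the schedules side by side, counts contacts, and adds an illustration on stated assumptions.

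**Step 1: specified contacts between randomisation and the month-3 assessment**

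| | TAU alone | Three active arms |
|---|---|---|
| Specified contact | Weekly, by an RA | Weekly session, by a therapist |
| Planned number | about 12 | 12 |
| Depends on attending therapy | No | Yes |
| General regular contact | Promised, no frequency | Promised, no frequency |
| Stated adverse event enquiry | None | None |

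Planned against planned, the arms are equal at about 12. The differences are in who makes the contact and what it depends on.

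**Step 2: contacts achieved in an active arm**

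Inputs: 12 weekly sessions (abstract) and the progression thresholds "> 60% of attendance, > 70% of adherence, < 30% of attrition" (Primary outcomes: feasibility indicators). Sessions attended = 12 × attendance.

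- 100%: 12 × 1.0 = 12
- 80%: 12 × 0.8 = 9.6
- 60% (the article's threshold): 12 × 0.6 = 7.2
- 40%: 12 × 0.4 = 4.8
- Complete non-attender: 0

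The unspecified regular contact comes on top of each figure. TAU calls can also fail to reach people, and the article gives no rate for that, so 12 is the planned TAU number and not an achieved one.

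**Step 3: what unequal detection would do to the counts**

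Assumptions, none from the article: the true risk of at least one adverse event is equal in both arms, and detection is 100% in one arm and 60% in the other. The arm size of 65 is from Sample size. Recorded = 65 × risk × detection.

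| True risk | Full detection | 60% detection |
|---|---|---|
| 10% | 65 × 0.10 = 6.5 | 6.5 × 0.6 = 3.9 |
| 20% | 65 × 0.20 = 13.0 | 13.0 × 0.6 = 7.8 |
| 30% | 65 × 0.30 = 19.5 | 19.5 × 0.6 = 11.7 |

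Either column could be TAU. A full therapy session may bring out more than a five-minute retention call, which would favour detection in the active arms. A missed session brings out nothing, which would favour detection in TAU. The direction is therefore unknown.

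**Step 4: is there a common collection point that removes the difference?**

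All arms are assessed at months 3 and 6 and contacted monthly between them, so the occasions exist. No adverse event enquiry is attached to any of them.

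**The case against.** The strongest reply is that this is a condensed article. A common adverse event form could well be in the full protocol, and its absence here is not a fault. The retention plan and the adverse event section also serve different purposes and do not contradict each other. That stands as far as it goes: a missing form alone would be no finding. What remains is the contact schedule that the article does fix, by arm, alongside its commitment to record events throughout.

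Several stronger readings are tempting, and the text does not support them.

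- A reader might infer that adverse events surface through RA calls in TAU and only through sessions in the active arms. No section says so. The calls are described as retention contacts, and the review of an event draws on participant and researcher or therapist without splitting by arm.
- A reader might infer that active-arm non-attenders have no scheduled contact. Every arm has the month-3 assessment, regular contact is promised to all, and the section on missing data aims to follow up those lost during the intervention. What is missing is a specified contact before month 3.
- A reader might infer that adverse reactions cannot be compared between arms because session timing cannot apply to TAU. Timing is only an example there, and relatedness is judged against the study as a whole, including assessment procedures.
- A reader might take 30% attrition of the 195 active-arm participants, 0.3 × 195 = 58.5, and set it against none in TAU. The 30% is an overall attrition figure and not a rate of leaving therapy. The same rate gives 0.3 × 65 = 19.5 in TAU.

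It is also fair that adverse events are neither a primary nor a secondary outcome and that the analysis is largely descriptive. This limits the consequence to the reading of harms and to safety oversight; power and sample size are untouched.

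**Conclusion.** The point holds in a limited form. In months 0–3 the article specifies weekly RA contact for TAU only, while the specified contact in the active arms is a therapist session that depends on attendance. No enquiry about adverse events common to the arms is set. Detection may therefore differ by arm, and it is least assured for active-arm participants who stop attending before the month-3 assessment.

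The size cannot be computed from the document. The contact count runs from equality at full attendance (12 v about 12) to 7.2 at the 60% threshold and 0 for a complete non-attender, before any unspecified contact. On the assumed detection rates, equal risks of 20% would be recorded as 13.0 v 7.8 participants per arm of 65, in either direction. The conclusion rests on the published contact schedule being the one followed and on adverse events being found mainly through contact. It is worth correcting before recruitment, since a definitive trial would inherit the method.

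**What to change.** Ask the same scripted adverse event question, on the same form and with the same recall period, in all four arms at points every arm already has: the month-3 and month-6 assessments and the monthly contacts in months 3–6. Base any between-arm harms summary on these answers. Report events volunteered at therapy sessions or weekly TAU calls separately. Give the DMEC all events by arm, whatever their judged relatedness.

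Reconcile the retention and risk management sections on what contact active-arm participants have in months 0–3 once they stop attending. The month-3 question makes the counts more comparable, but does not by itself bring earlier events to light sooner.

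Calls triggered by missed sessions are not the answer. They would occur only in the active arms, so they would create a new difference in ascertainment, and they could prompt attendance, a primary feasibility outcome with its own threshold.

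The cost is one short form and a few minutes per contact. The script needs care so that the answers do not reveal the allocation to blinded assessors. The article reports that recruitment had not begun, so the change could be made in time.

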### Data management

The data will be collected by trained RA’s to maintain confidentiality and anonymity. Only essential personal identifiable data will be collected in consent forms. Study data will be stored according to the General Data Protection Regulations 2018, with personal identifiable data secured separately. Electronic data will be stored in password protected computers. Demographic and questionnaire data will be anonymised immediately after collection and inputted into a study-specific password protected database. Paper copies of questionnaires and consent forms will be stored in locked cabinets. Personal identifiable data will be kept locked away, separate from other research data. Access to both hard copies and electronic versions of data will be restricted to only designated persons as approved by the site principal investigator (PI). A signed duty log will be used to access the data.

### Confidentiality

Participant’s confidentiality will be protected by assigning a unique study number and use of pseudonyms on all research material, e.g., transcripts. Reporting of verbatim quotations in presentations and publications will be carefully reviewed by the research team in advance. Paraphrasing will be used if there is any risk of identification of participants or third parties. The participants would be verbally informed of the possibility of confidentiality being broken in certain circumstances, prior to consent being sought. With participants’ consent, we will digitally record some of intervention session randomly to improve quality in clinical supervision. Recordings will be made on an encrypted digital voice recorder and uploaded to a password protected computer as soon as possible after completion. Recordings will be deleted from the recorder after uploading and destroyed in the presence of two researchers, after completion of analysis.

### Plans for collection, laboratory evaluation and storage of biological specimens for genetic or molecular analysis in this trial/future use

Not applicable.

### Data analysis

#### Statistical analysis

The study data will be analysed using SPSS (Version-22). Analysis of data will take place after full recruitment and data collection. Descriptive data analysis will be performed to summarise demographic data and feasibility outcomes. Baseline and outcome assessment data will be summarised using the appropriate descriptive statistics and graphical summaries. As this is a feasibility study, the analysis of the data will be largely descriptive and will focus on confidence intervals for the difference amongst groups for each outcome measure. Possible between-group differences will be assessed using analysis of variance (ANOVA) and chi-square tests. The results of the trial will follow the standard CONSORT recommendations. A complete statistical analysis plan will be written prior to database lock and subsequently will be discussed and approved by the Trial Steering Committee (TSC). There is no interim analysis planned.

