## Methods

### Study design and setting

This will be a four-arm feasibility factorial RCT. An overview of complete study design is provided in Fig. 1. The proposed project will consist of three phases. The first phase of the study will focus on the adaptation/development of the intervention in accordance with the Pakistani culture. The second phase will include refinement of the interventions and production of the intervention manuals. The third phase will be to assess the feasibility through a factorial RCT. The study will be carried out in Karachi, Hyderabad, Peshawar, Lahore and Rawalpindi, Pakistan. Recruitment of participants will be from primary care and volunteer organisations/drug rehabilitation centres.

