### Phase 3: feasibility factorial RCT

The feasibility of the intervention will be assessed using a factorial RCT, for MICBT and MBRP intervention, comparing four groups: (1) MICBT plus treatment as usual group (TAU), (2) MBRP plus TAU group, (3) the integrated MICBT and MBRP with TAU and (4) TAU group alone. In Pakistani culture, people consider themselves more as part of a family and larger community rather than as individuals. Therefore, a group approach is more culturally appropriate but for certain private/family issues the flexibility of some individual time with the therapists will be offered. The group sessions will consist of approximately eight participants.

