#### Sample size

Based on the recommendations by Sim and Lewis [45], a minimum sample size of at least 50 participants per group is required for feasibility studies. Assuming 30% attrition rate, we aim to recruit a total of *N* = 260 participants, with 65 participants randomised to each arm according to 2 × 2 factorial design scheduled in given Table 2.

**Table 2 Tab2:** 2 × 2 Factorial design schedule of intervention with sample size

	TAU	MBRP	Total
MICBT	65	65	130
TAU	65	65	130
Total	130	130	260

The findings of this feasibility study will help determine the initial data for the outcome measures and will help in providing a sample size estimate for a larger future definitive trial; therefore, no formal power calculations have been undertaken.

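### The stated ANOVA names no baseline covariate and no factorial terms, although this 2 × 2 factorial trial measures its continuous secondary scores at baseline

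*Protocol article*

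**What the plan says.** All places are in the protocol article.

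- **Design.** Study design and setting: "This will be a four-arm feasibility factorial RCT". Sample size gives the allocation, "with 65 participants randomised to each arm", and Table 2 prints the factorial layout with margins of 130 and 130 for each component.
- **Comparison.** Phase 3: feasibility factorial RCT describes the trial as "comparing four groups": each component with usual care, the two combined, and usual care alone.
- **Analysis.** Statistical analysis states that the work "will focus on confidence intervals for the difference amongst groups for each outcome measure". It then says: "Possible between-group differences will be assessed using analysis of variance (ANOVA) and chi-square tests". No covariate, main effect, interaction or marginal contrast is named, and the text does not say whether the ANOVA is one-way or two-way.
- **Baseline data.** Data collection method: all participants "will undergo assessments at baseline, 3rd month (end of intervention) and at 6th month after randomisation", with MAP, SWEMWBS and EQ-5D among the instruments.
- **Where baseline is used.** In descriptive summaries (Statistical analysis), as predictors in the missing-data weights (Statistical methods to handle missing data), and in an EQ-5D change score (Health economics). None of these is described as baseline adjustment of the between-group comparison.
- **Purpose of the estimates.** Statistical methods to handle missing data says that effect sizes from this trial will feed the power calculation of a larger one.

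**The concern.** The Statistical analysis section commits itself to an estimate and to tests, so this is a stated choice and not only a gap. On the outcomes where it matters, the choice leaves two things unused.

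The first is the baseline score. A plain ANOVA of follow-up values carries any chance baseline difference between arms into the estimate, and it leaves in the residual all the variance that the baseline would explain. Intervals are the declared focus of the analysis, so their width matters here.

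The second is the factorial structure. Whoever plans a later factorial trial wants the effect of each component and some view of whether the two combine additively. The text does not promise any of these. If the ANOVA is run across four unstructured groups, the reader receives arm-against-arm differences and must rebuild the component effects.

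**Working it through.** **Inputs from the article.** 65 per arm and 260 in total; 30% attrition; three assessments with the same scales (Sample size; Data collection method).

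**Assumptions, because the article gives no figure.** 95% intervals; outcomes in SD units with equal variance; equal losses across arms; an unweighted analysis; baseline-to-follow-up correlation r between 0.3 and 0.6.

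**1. The article's own figure.** It takes "a minimum sample size of at least 50 participants per group is required for feasibility studies", and 50 × 1.30 = 65 per arm, 4 × 65 = 260. That reproduces the stated size. Losing 30% of 65 leaves 65 × 0.70 = 45.5 per arm and 182 in total, the numbers used below. (Dividing instead, 50 / 0.70 gives 72 per arm. That is a separate matter and does not bear on this point.)

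**2. Cost of omitting the baseline value, same contrast.** Adjusting for baseline multiplies the residual SD by √(1 − r²), so the unadjusted interval is wider by 1/√(1 − r²):

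| r (assumed) | √(1 − r²) | unadjusted / adjusted width |
|---|---|---|
| 0.3 | 0.954 | 1.05 |
| 0.5 | 0.866 | 1.15 |
| 0.6 | 0.800 | 1.25 |

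This ratio does not depend on the sample size (one degree of freedom is negligible here) or on which contrast is taken. At r = 0 there is no gain.

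**3. Arm-against-arm contrast and marginal contrast, unadjusted.** Half-width = t × √(2/n), with n per side of the contrast. With 182 analysed and four means fitted there are 178 degrees of freedom, so t = 1.973.

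- One arm against another: n = 45.5, 1.973 × √(2/45.5) = 0.414 SD.
- Component present against absent: n = 2 × 45.5 = 91, 1.973 × √(2/91) = 0.293 SD.
- Ratio: √2 = 1.41.

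These estimate the same quantity only if the components do not interact.

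**4. The interaction.** As a difference of differences over four cells, its half-width is t × √(4/45.5) = 1.973 × 0.2965 = 0.585 SD unadjusted. It can be estimated, but imprecisely. Baseline adjustment at r = 0.5 brings it to 0.507 SD.

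**The case against.** The strongest reply is that this is a condensed article for a feasibility trial. It calls its analysis largely descriptive and promises a full analysis plan before database lock. Its progression criteria do not rest on between-group scores. Model terms are ordinary analysis-plan content, and ANOVA of a 2 × 2 layout may well mean a two-way ANOVA, which gives both main effects and the interaction.

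Much of this stands, and it limits the point. A reader might infer three stronger claims that the article does not support:

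- **That the plan discards the factorial margins.** The text is silent on this. The four-group phrase in Phase 3 lists the arms and does not specify a model. Even a one-way fit keeps the four cell means, from which the interaction can be calculated.
- **That every interval is too wide.** Recruitment, retention, attendance, adherence and satisfaction have no baseline value, and session attendance does not exist in the arm with usual care alone. The precision point concerns continuous secondary scores only.
- **That the planned intervals are about 1.6 times as wide as they need be.** That ratio (0.414 / 0.253 = 1.64) sets an unadjusted arm-against-arm contrast beside a marginal effect adjusted at r = 0.5. It mixes two different estimands with an assumed correlation. The like-for-like loss is the 1.05 to 1.25 in step 2.

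The reply does not remove the baseline point. The article names its test, and neither one-way nor two-way ANOVA as named carries a covariate. Using baseline variables to weight for missing outcomes, or taking an EQ-5D change score for the economic work, does not adjust the comparison of arms.

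**Conclusion.** The point holds for the continuous secondary scores measured at baseline: SWEMWBS, EQ-5D and those MAP scores that are analysed as continuous.

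- **Baseline.** The stated method omits the adjustment. Intervals are about 1.05, 1.15 or 1.25 times as wide as the adjusted ones at r = 0.3, 0.5 or 0.6, and chance imbalance stays in the estimates. The correlation is an assumption. It may be low for some scores, and the gain shrinks with it.
- **Factorial terms.** This part is conditional. If the ANOVA is one-way, the component effects at the margins are not reported, although without interaction they would be estimated to about ±0.29 SD, against ±0.41 SD for an arm-against-arm contrast, with 182 analysed. If a two-way ANOVA is meant, the article should say so.

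The change should be made because the article wants these effect sizes for planning a larger trial. It does not affect the feasibility conclusions or the progression criteria.

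**What to change.** For continuous scores measured at baseline, replace ANOVA with a two-factor ANCOVA at each follow-up, or its mixed-model form:

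*outcome = MICBT (yes/no) + MBRP (yes/no) + MICBT × MBRP + baseline value of the same score*

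Report both marginal effects, the interaction with its interval (noting that it is imprecise, about ±0.585 SD unadjusted with 182 analysed), and the four adjusted cell means. The planned missing-data weights can be carried into the same model. If contrasts among four groups are wanted instead, say why, and still adjust for baseline. A city term is optional, since Sequence generation names no stratification by city. Leave the primary feasibility outcomes as they are.

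The cost is wording in the analysis plan, which the article says is to be written before database lock. No data are added. The downside is that marginal effects need cautious reading if the components interact, which is why the cell means are reported beside them.
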